### Experimental and clinical protocol

Patients will be recruited from a residential cardiovascular rehabilitation unit in the northwestern of Italy. The cardiac rehabilitation (CR) program lasts 1 month for each patients in accordance with the Italian Health Institute's guidelines. Along this period, patients live in the S. Giuseppe hospital, which is located on a mountain highland and far away from towns and cities. Few days after entry in the CR unit and immediately after the initial medical evaluation and treatment planning (first week), patients will be approached by the research investigator for initial screening in accordance to inclusion and exclusion criteria. Patients who will go through the screening will be informed orally by the research investigator that a scientific study is ongoing and that its purpose is "to learn more about how individuals adjust to having heart disease". They will be also told that they could be asked to write about their experiences with heart disease and, if they will consent, they will be scheduled for the following day when they will receive the informed consent form, which includes no mention of expected benefits from the writing sessions and no mention of the randomization to one of four conditions. Once patients will have signed the informed consent form, they will be administered the baseline questionnaires. With the exception of the control participants, they will receive a schedule relative to the four writing sessions to be completed within the following two weeks. Once randomization will be performed, no change in treatment allocation will take place in the future. Participants will complete the individual writing sessions in a peaceful laboratory close to the CR unit. Writing instructions will be written on the sheets that patients will use to write and will be presented to them at the beginning of each writing session. A research assistant will meet with each participant just before writing, will give him the writing sheets and will let him alone in the laboratory for twenty minutes, then she will return to stop the session and to pick up the sheets.

Participants will be randomized to one of the following four conditions: 1) disease-related expressive writing (DS-EW); 2) standard expressive writing (S-EW); 3) unemotional writing (Sham) and 4) an empty condition not involving a writing task (assessments only). All the active conditions (1, 2 and 3) will consist in four 20-minute writing sessions that will occur during the hospital stay within a 2-week period and that will be scheduled twice a week for each participant.

Writing instructions for the three active groups will be as follows:

At the end of the CR program and before discharge, all participants, including those assigned to the empty control condition, will be re-administered the outcome questionnaires and will be told that they will receive other follow-up questionnaires by mail at 3, 6, 9 and 12 months after discharge from hospital. A form on which to record any medical visits or events over the previous 3 months will be also sent at each participant at each follow-up assessment.

#### 1. Disease-related expressive writing (DS-EW)

"What I would like you to write about for these four sessions are your deepest thoughts and feelings about your experience with heart disease. I realize that individuals with heart disease experience a full range of emotions and I want you to focus on any and all of them. In your writing, I want you to really let go and explore your very deepest emotions and thoughts. You might think about all the various feelings and changes that you experienced before being diagnosed, after diagnosis, during treatment, and now. Whatever you choose to write, it is critical that you really focus on your deepest thoughts and feelings. Ideally, I would like you to focus on feelings, thoughts or changes that you have not discussed in great detail with others. You might also tie your thoughts and feelings about your experiences with heart disease to other parts of your life - your childhood, people you love, who you are or who you want to be. Again, the most important part of your writing is that you really focus on your deepest emotions and thoughts. The only rule we have is that you write continuously for the entire time. If you run out of things to say, just repeat what you have already written. Don't worry about grammar, spelling or sentence structure. Don't worry about erasing or crossing things out. Just write."

#### 2. Standard expressive writing (S-EW)

"What I would like you to write about for these four sessions are your deepest thoughts and feelings about the most traumatic or negative experiences you had in your life. I realize that individuals who live a traumatic experience have a full range of emotions and I want you to focus on any and all of them. In your writing, I want you to really let go and explore your very deepest emotions and thoughts. Whatever you choose to write, it is critical that you really focus on your deepest thoughts and feelings. Ideally, I would like you to focus on feelings, thoughts or changes that you have not discussed in great detail with others. You might also tie your thoughts and feelings about your negative experiences to other parts of your life - your childhood, people you love, who you are or who you want to be. Again, the most important part of your writing is that you really focus on your deepest emotions and thoughts. The only rule we have is that you write continuously for the entire time. If you run out of things to say, just repeat what you have already written. Don't worry about grammar, spelling or sentence structure. Don't worry about erasing or crossing things out. Just write."

#### 3. Unemotional writing (Sham)

"What I would like you to write about for these four sessions is a detailed account of facts regarding your heart disease and its treatment. I am interested in how the specifics of detection, diagnosis and treatment differ among individuals with heart disease; therefore, it is critical that you provide an extremely detailed account of all that happened to you with regard to having heart disease. I realize that individuals with heart disease experience many emotions, but in your writing I want you to focus only on the facts, not on your emotions. No fact is too big or too small. You might write about when your hear disease was discovered and who discovered it, appointments that you had with doctors or other people about your heart disease, information you were given and what treatment was chosen. You might recount your experience from beginning to present day, including all the factual details you can think of. Again the most important part of your writing is that you focus on the facts and try to reconstruct what happened in as great factual detail as possible. The only other rule ... [Instructions continue as above]

### Outcome Measures

#### SF-12

The SF-12 Health Survey is a measure of physical and mental health. It is the short form of the most popular SF-36 and consists of the 12 items that were found to be the best predictors of the two SF-36 physical and mental summary scores (referred to as PCS-36 and MCS-36, respectively) in the US validation study [39]. Selected items and weights derived from the general US population were then used to score the physical and mental summary scores (referred to as PCS-12 and MCS-12, respectively). The PCS-12 and MCS-12 were very highly correlated with PCS-36 and MCS-36 (r = 0.951 and 0.969, respectively) and were very weakly correlated (r = 0.06) with each other in the US sample. In the present study, the Italian version of the SF-12 will be used [40] and the two summary scores (PSC-12 and MCS-12) will be computed with weights derived from the Italian validation sample.

#### Beck Depression Inventory - II

The Beck Depression Inventory - Second Edition (BDI-II) is a measure of depressive symptoms. It was developed by revising the BDI in response to the American Psychiatric Association's publication of the Diagnostic and Statistical Manual of Mental Disorders, Fourth Edition, which changed many of the diagnostic criteria for Major Depressive Disorder. Indeed, the BDI items involving changes in body image, hypochondria and difficulty working were replaced. Also, sleep loss and appetite loss items were revised to assess both increases and decreases in sleep and appetite. All but three of the items were reworded; only the items dealing with feelings of being punished, thoughts about suicide and interest in sex remained the same. Finally, respondents rate how they have been feeling for the past two weeks, as opposed to the past week as in the original BDI. Like the BDI, the BDI-II also contains 21 items and each answer is scored on a scale that ranges from 0 to 3. A total score is computed by summing all the ratings and higher total scores indicate more and more acute depressive symptoms. The Italian study to establish the validity and reliability of the measure indicated that the BDI-II is positively correlated with the Hamilton Depression Rating Scale. The test was also shown to have a high one-week test-retest reliability (Pearson r = 0.93), suggesting that it was not overly sensitive to daily variations in mood. The test also has high internal consistency (α = .91).

#### Beck Anxiety Inventory

The Beck Anxiety Inventory (BAI) is a measure of anxiety symptoms. It consists of 21 items that represent 21 psychological or somatic symptoms of anxiety (such as numbness, hot and cold sweats or feelings of dread). The respondent is asked to rate on a scale which ranges from 0 (*Not at all*) to 4 (*SEVERELY: I could barely stand it*) how each symptom has caused him distress in the previous week. A total score is computed by summing all the ratings and higher total scores indicate more and more severe anxiety symptoms.

#### Post-Traumatic Growth Inventory - Short Form

The Post-Traumatic Growth Inventory - Short Form (PTGY-SF) was derived analytically from the 21-item PTGY [41] and consists of the 10 items that loaded most on each of the five underlying factors [42]. In particular, the items with the highest loadings on each factor were examined and the two with the highest loadings were selected for three (Spiritual Change, Appreciation of Life and Personal Strength) of the five factors. For the remaining two factors (Relating to Others and New Possibilities) the two items with the highest loadings were not selected because they were too redundant in content; instead items were selected in order to improve the breadth of coverage. In the US validation study, the 10-item PTGI-SF had internal reliability only very slightly lower than the full form PTGI, and the reliability of the total score was generally in the range of .90 across a variety of samples [42]. In the present study, the Italian translation of the PTGY-SF 10 items were used [43] and a total score for each participant was computed by averaging the responses to all the items.

#### Frequency of medical visits for cardiovascular morbidity

A form on which to record any medical visits over the previous 3 months will be also sent at each participant at the four follow-up time points. Patients have to retrospectively record all medical visits during the previous 3 months. They have to record also the medical provider and the reason for each visit (e.g., check-up with medical cardiologist). These medical appointments will be coded as a function of reason for the visit (i.e., routine and non-routine CVD-related and non-CVD-related appointments) by the research investigator who will be aware of participants' condition assignment. Medical appointments for CVD-related problems will be of interest, excluding scheduled check-ups, as an indicator of morbidity associated with CVD and its treatment. The other categories of medical appointments (i.e., CVD-related scheduled medical check-ups, other scheduled medical check-ups or non-routine medical appointments for other problems, such as flu symptoms) will be combined for analysis.

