**Methods:**

The clinical effectiveness of a 2-week disease-related expressive writing procedure (writing about one's deepest thoughts and feelings regarding the experience with heart disease) compared with the standard writing task (writing about one's deepest thoughts and feelings about the most traumatic or negative event experienced in the life), a neutral writing condition (writing about the facts regarding heart disease and its treatment) and an empty control condition will be evaluated in a randomized controlled clinical trial (RCT) with repeated follow-up measurements at 3, 6 and 12 months after discharge from CR. The primary outcome is health-related quality of life (SF-12). Secondary outcome measures are depression (BDI-II), anxiety (BAI) and post-traumatic growth (PTGI). Furthermore, the study will explore the moderating effects of coping styles, type D personality, perceived emotional support and participants' evaluative ratings of the writing interventions on the main experimental effects in order to identify sub-groups of patients showing different results.

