## Methods

### Study design

A four-arm randomized controlled clinical trial with four follow-up assessments (immediately before discharge from hospital, 3 months, 6 months and 12 months after discharge) will be carried out in order to test the following primary hypotheses/outcomes: 1) a modified disease-related expressive writing intervention is effective in enhancing physical and psychological health outcomes (HRQoL, anxiety and depression symptoms, medical visits for CVD-related morbidities) relative to a sham condition in which patients write solely about the facts of their experience with CVD and relative to a control empty condition; 2) the modified disease-related expressive writing intervention is more effective in enhancing physical and psychological health outcomes than a standard expressive writing condition in which patients write about the their deepest thoughts and feelings about the most traumatic or negative event they have experienced in their life. Further hypotheses/outcomes concern post-traumatic growth and are: 1) the modified disease-related expressive writing intervention is effective in enhancing post-traumatic growth relative to sham and control conditions; 2) the modified disease-related expressive writing intervention is more effective in enhancing post-traumatic growth than the standard expressive writing task.

Secondary analyses will be conducted in order to explore the relative efficacy of the writing conditions as a function of patients' gender, age, coping styles, negative affectivity and social constraint (type D personality factors), perceived social support and evaluative ratings of the writing intervention. Accordingly, significant interactions between the experimental conditions and the moderator variables mentioned above are postulated such that, for example, patients low on avoidance will benefit more from expressive writing than avoidant patients and that patients perceiving low social support will benefit more than patients perceiving high social support.

The Medical Ethics Committee of Istituto Auxologico Italiano approved the study protocol.

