### Statistical analysis

Data entry will be conducted by a trained research assistant who will be aware of participants' condition assignment but not of the research hypotheses. Preliminary analyses will be performed to examine assumptions for parametric statistical analysis and baseline equivalence among groups. Given the longitudinal nature of the data (repeated measurements), multilevel modeling analysis in MLwiN 2.21 (Centre for Multilevel Modeling-CMM, University of Bristol) will be used to study health outcomes (physical and mental health, anxiety, depression, post-traumatic growth and number of medical visits for cardiovascular morbidity) as functions of time and experimental conditions. This will allow testing of experimental hypothesis as cross-level interactions between slopes representing time (1^th ^level) coded as 0 for the first (immediately before discharge from hospital) follow-up, as 1 for the second (3-month) follow-up, as 2 for the third (6-month) follow-up and as 3 for the fourth (12-month) follow-up, and a categorical covariate representing conditions (2^nd ^level). We will start with a simple random intercept model (for calculating intra-class correlation [ICC]) and a simple linear growth model, followed by a model with experimental conditions as a time-invariant covariate. We then will structure more complicated models, including models with different within-individual covariance structures and models with nonlinear growth patterns. A critical alpha of 0.05 will be considered for hypothesis testing. Furthermore, on the basis of the best multilevel models structured in the primary analyses, we will explore the moderating effects of some putative covariates at level 2 such as gender, age, coping styles, negative affectivity and social inhibition (Type D personality dimensions), perceived social support and writings ratings. For these secondary explorative analyses no level of significance will be defined. Readers interested in further discussion of analyzing longitudinal data with multilevel modeling analysis are referred to an excellent guide by Kwok et al. [48] as well as a thorough treatment of the issue by Singer and Willett [49].

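### The follow-up schedule contradicts itself (3, 6, 12 versus 3, 6, 9, 12 months), so the three-month visit form either misses months 6 to 9 or yields a 9-month wave that the model does not code

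*Protocol article*

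**What the plan says.** Three places in the protocol article give one schedule:

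- Abstract, Methods: "repeated follow-up measurements at 3, 6 and 12 months after discharge from CR".
- Study design: "four follow-up assessments (immediately before discharge from hospital, 3 months, 6 months and 12 months after discharge".
- Statistical analysis: the same four waves, with discharge "coded as 0 for the first (immediately before discharge from hospital) follow-up" and codes 1, 2 and 3 for 3, 6 and 12 months.

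Experimental and clinical protocol gives another. Patients repeat the outcome questionnaires before discharge and are told that "they will receive other follow-up questionnaires by mail at 3, 6, 9 and 12 months after discharge from hospital". The same paragraph sends "A form on which to record any medical visits or events over the previous 3 months" with each follow-up assessment.

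The section on frequency of medical visits says that the form "will be also sent at each participant at the four follow-up time points", without naming the months, and fixes the look-back: "Patients have to retrospectively record all medical visits during the previous 3 months".

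Statistical analysis lists the number of cardiovascular visits among the outcomes modelled by time and condition. Study design names visits within its first hypothesis. The Discussion sets physiological measures aside and keeps medical visits or events as the only biomedical indicator. The Abstract names the SF-12 as primary and depression, anxiety and post-traumatic growth as secondary; visits are not in that list.

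**The concern.** A count with a three-month look-back describes the whole follow-up only if forms arrive every three months. One of the two schedules meets that condition and the other does not. The schedule that meets it is not the one that the analysis section codes. Staff who mail according to Experimental and clinical protocol would therefore collect data for which the analyst has no time code. An analyst who follows Statistical analysis would expect a visit count at discharge that no mailed form supplies.

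At stake is the only biomedical outcome that the plan keeps. A window not asked about at the time can be recovered later only by longer recall. The 9-month conflict also reaches the questionnaires, because the sentence that promises a 9-month mailing speaks of follow-up questionnaires in general.

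**Working it through.** The plan gives no coverage figure to reproduce. Its sample size rests on an assumed effect on quality of life and is not affected by this point.

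**Inputs.** Look-back of 3 months (Experimental and clinical protocol; Frequency of medical visits). Schedule A: 3, 6 and 12 months (Abstract; Study design; Statistical analysis). Schedule B: 3, 6, 9 and 12 months (Experimental and clinical protocol). Time codes 0 to 3 for discharge, 3, 6 and 12 months (Statistical analysis).

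**Number of waves after baseline.** A: discharge + 3 = 4. B: discharge + 4 mailed = 5.

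**Coverage.** A form at month t with look-back w covers t − w to t.

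- Schedule A: 0–3, 3–6 and 9–12, so 3 × 3 = 9 of 12 months (75%). Months 6 to 9 are missed: 3/12 = 25%. The 12-month form covers 3 of the 6 months since the previous form.
- Schedule B: 0–3, 3–6, 6–9 and 9–12, so 4 × 3 = 12 of 12 months.

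**Match to the model.**

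| Wave | Time code | Visit window, schedule A | Visit window, schedule B |
|---|---|---|---|
| Discharge | 0 | only if a form is completed then | no mailed form |
| 3 months | 1 | 0–3 | 0–3 |
| 6 months | 2 | 3–6 | 3–6 |
| 9 months | none | none | 6–9 |
| 12 months | 3 | 9–12 | 9–12 |

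Under A, three months have no record. Under B, one window has no code and one code has no mailed count. Neither schedule makes the collection and analysis sections agree for visits.

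**Discharge form (conditional).** Suppose that the four unnamed time points for the form are the four assessments in Study design. A form at discharge then looks back about 13 weeks. Screening is in the first week and allocation follows the baseline measurements, so I assume randomisation at about the end of week 1. The stay is given as 3 weeks in the Discussion and 1 month (about 4 weeks) in Experimental and clinical protocol.

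- 3-week stay: (3 − 1)/13 = 2/13 = 15% of the window after randomisation.
- 4-week stay: (4 − 1)/13 = 3/13 = 23%.

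On this reading, 77% to 85% of the time-0 window lies before allocation.

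**The case against.** The strongest reply is that the visit form probably belongs to the mailed waves only. It is described as sent, directly after the sentence that lists four mailed follow-ups, whereas the discharge questionnaires are completed on site. On that reading the four time points for the form are 3, 6, 9 and 12 months, coverage is complete and there is no discharge form. This is a fair reading, and it is why the discharge point is only conditional. It does not rescue the analysis section, which still lacks a code for month 9 and still starts visits at a discharge wave without a mailed count. Nor does it explain why the Abstract and Study design omit month 9.

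Two further replies stand. Even under 3, 6 and 12 months, each post-discharge form covers an equal three-month window, so the counts stay comparable across waves and arms. And visits lie outside the Abstract's list of primary and secondary outcomes, which limits the weight of the point.

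A reader might also infer from "a simple random intercept model (for calculating intra-class correlation [ICC]) and a simple linear growth model" that a sparse count is to be analysed as normally distributed. The document does not support this. It states no distribution or link for any outcome, allows for more complex models, and gives no visit rate from which sparseness could be judged. The choice of distribution is commonly left to an analysis plan, which is not shown.

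**Conclusion.** The contradiction is in the current text and nothing in the document resolves it. Its consequence depends on the schedule followed: 3 of 12 post-discharge months unrecorded (25%), or full coverage with an uncoded 9-month wave and no mailed visit count at time 0. These results need only the stated look-back, schedules and time codes.

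The statement that only 15% to 23% of a discharge window follows randomisation rests on three assumptions: that a discharge form exists, that allocation is at about week 1, and that the stay is 3 to 4 weeks. If they hold, that count should not be treated as a post-intervention outcome.

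Two stronger conclusions are tempting. One is that the missing quarter biases the comparison; but the gap is the same in all arms, so by itself it costs information and blurs the definition of the outcome. The other is that a discharge count dilutes the treatment effect. That is not shown: the hypotheses are tested as condition-by-time interactions with discharge as the starting point, where a mostly pre-randomisation count may act largely as an anchor. The point should be fixed, but it does not undermine the primary SF-12 comparison through the recall window.

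**What to change.** 1. State one schedule and use it in the Abstract, Study design, Experimental and clinical protocol, Frequency of medical visits and Statistical analysis. Name the months at which the visit form is sent.
2. Close the gap in one of two ways:
   - Keep the 9-month visit form, already announced to patients in Experimental and clinical protocol. The cost is one mailed page.
   - Have the 12-month form ask about the previous 6 months. The cost is one reworded question, with poorer recall and unequal windows that the analysis must account for by the months that each count covers.
3. Give visits time codes that match the waves at which they are collected. Say whether the questionnaires are also collected at 9 months and, if so, code that wave.
4. If visits are recorded at discharge, use that count only as a baseline covariate. Its window is best worded to end at admission, since otherwise a small part of it follows randomisation.

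In all, this is one form and a few sentences.

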### Randomization procedure and blinding

All participants will be randomly assigned to the experimental conditions in a consecutive way. The simple randomization scheme will be generated by using the Web site http://www.randomization.com. Random allocation will take place after the baseline measurements and patients will be blind to condition assignment.

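### Visits are sorted into CVD-morbidity visits by an investigator who knows each patient's arm, so every between-arm contrast on visits is open to differential classification

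*Protocol article*

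**What the plan says.** All references are to the protocol article.

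- **Source of the data** (*Frequency of medical visits for cardiovascular morbidity*): "Patients have to retrospectively record all medical visits during the previous 3 months". They also give the provider and the reason for each visit.
- **Sorting** (same section): visits are coded as "routine and non-routine CVD-related and non-CVD-related appointments", and this is done "by the research investigator who will be aware of participants' condition assignment".
- **What the sorting decides** (same section): "Medical appointments for CVD-related problems will be of interest, excluding scheduled check-ups, as an indicator of morbidity associated with CVD and its treatment". All other visit categories are pooled.
- **Standing of the outcome:** *Study design* puts it within the primary hypotheses, in the list "HRQoL, anxiety and depression symptoms, medical visits for CVD-related morbidities". The Abstract names the SF-12 as primary and depression, anxiety and post-traumatic growth as secondary, and visits are in neither group. The *Discussion* leaves physiological measures out and uses visits or events as the only stand-in for bio-medical health. *Statistical analysis* models the number of visits by time and condition, with an alpha of 0.05.
- **Masking elsewhere:** under *Experimental manipulation check*, the essays are rated by an independent person who does not know the condition. Under *Statistical analysis*, "Data entry will be conducted by a trained research assistant who will be aware of participants' condition assignment", and the same sentence adds that this assistant does not know the hypotheses.
- **Patients:** *Randomization procedure and blinding* states that "patients will be blind to condition assignment". *Experimental and clinical protocol* says that the consent form mentions neither the randomization to four conditions nor any expected benefit, that patients are told they might be asked to write, and that one of the four arms has assessments only.

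**The concern.** Whether a visit was routine, and whether it was for a cardiovascular problem, has to be decided from a patient's short recalled entry. That decision puts the visit into the morbidity count or leaves it out. If the coder knows the arm, borderline entries can be resolved differently by arm without any intent to do so. The result is bias and not noise: a larger sample does not reduce it, and no feature of the multilevel model removes it. It can affect every contrast on visits, including disease-related writing against sham and against standard expressive writing.

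At stake is the trial's only bio-medical marker. A difference in visits, or the absence of one, could be attributed to the coding, and the trial would have no masked data with which to answer.

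A smaller matter lies beside it. The statement that patients are blind is unqualified, yet patients in the empty arm know that they do not write. The SF-12, BDI-II, BAI, PTGI and visit records are all self-reported, so contrasts with that arm lack part of the protection that the sentence implies.

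**Working it through.** **1. Does the coder's knowledge reach the outcome?** Patients supply raw entries. The coder assigns two attributes to each, routine or not and CVD-related or not. Only one combination, CVD-related and not a scheduled check-up, forms the morbidity count. The person assigning the attributes is stated to know the arm. No later step in the article corrects this.

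**2. Is masking feasible within this plan?** The manipulation check already uses a rater unaware of condition, and for data entry the plan notes that the assistant does not know the hypotheses. No comparable safeguard is stated for visit coding. The visit forms come back on paper by mail, so they can be labelled with a study number alone.

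**3. The plan's own figures.** The plan gives no expected visit rate, no qualifying share and no effect on visits, so there is no figure on this outcome to reproduce. Its one design figure concerns quality of life: 92 patients, 23 per arm, f = 0.4, power 0.82. It reproduces. In a four-group one-way ANOVA with 19 evaluable per arm, the noncentrality is 0.4² × 76 = 12.16 and power is 0.823; 76 × 1.2 = 91.2, which rounds up to 92. It serves here only to set the arm size: 23 × 0.8 = 18.4, so about 18 per arm after the planned dropout.

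**4. Illustration of size. Every input in this step except the arm size is an assumption.** Let a share s = 30% of visits truly qualify in each arm, with no true effect.

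*Rate ratio.* If coding lowers the share by d in one arm only, the ratio is (s − d)/s. If it moves both arms in opposite directions, the ratio is (s − d)/(s + d).

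| Coding shift | Shares compared | Rate ratio |
|---|---|---|
| 1 point each way | 29% / 31% | 0.94 |
| 3 points each way | 27% / 33% | 0.82 |
| 5 points, one arm | 25% / 30% | 0.83 |
| 10 points, one arm | 20% / 30% | 0.67 |

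*False-positive rate.* Take Poisson counts a and b in two arms of n patients with m visits each, and reject when |a − b|/√(a + b) > 1.96. For n = 18, m = 4 and a 5-point shift in one arm, the expected counts are 18 × 4 × 0.30 = 21.6 and 18 × 4 × 0.25 = 18.0. The expected statistic is 3.6/√39.6 = 0.57 instead of 0. Simulation with 200,000 replicates per row gave:

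| Patients per arm | Visits per patient | No shift | 5 points | 10 points |
|---|---|---|---|---|
| 18 | 4 | 5.0% | 8.6% | 22.4% |
| 18 | 8 | 5.0% | 12.7% | 39.9% |
| 23 | 4 | 4.9% | 9.7% | 27.1% |
| 23 | 8 | 5.0% | 15.1% | 48.6% |

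The larger arms do worse because the bias stays fixed while the standard error falls. Real visit counts usually vary more than Poisson counts. A test that allows for this would show less inflation, but the distortion of the rate ratio would be the same.

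**5. Patient blinding, with the statements side by side.** One section says that patients do not know their condition. Another withholds the randomization, and with it the existence of other conditions, as well as the expected benefits. A third gives one arm no writing, after all patients have been told that they might be asked to write. The statement is therefore defensible among the three writing arms. For the empty arm it holds only in the sense that patients do not know they are controls in a four-arm trial.

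**The case against.** The best reply on the coding is that it leaves limited room for judgement. Patients must state the provider and the reason, the categories are defined, and scheduled check-ups are excluded by rule. This stands as a reason to expect small shifts. It does not remove the problem, because unclear or mixed reasons still have to be resolved by someone who knows the arm. It is also fair to say that the illustration restates assumed inputs and measures nothing about this trial. That stands in full.

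Several stronger readings are tempting, and the article does not support them:

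- *The trial's main result is compromised.* Coding cannot touch the SF-12, BDI-II, BAI or PTGI, the Abstract names the SF-12 as primary, and the sample size rests on quality of life.
- *The coder knows the hypotheses.* This is plausible for a research investigator but is not stated. Knowledge of the arm is stated, and it is enough for the point.
- *Data entry is equally exposed.* The article says that the assistant who enters the data does not know the hypotheses, and entering data requires far less judgement than sorting visits.
- *Contrasts with the empty arm are open comparisons.* The consent form withholds the randomization and the expected benefits. Knowing that one is not writing is less than knowing that one is a control.
- *Disease-related writing against sham should therefore carry the conclusion.* That would alter the objectives in *Study design*, which also include the empty control and standard expressive writing. It would not help with coding either, since that contrast is exposed in the same way.

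**Conclusion.** The point holds for the visits outcome. The article states outright that the classification which forms the CVD-morbidity count is made by someone who knows the arm, and every between-arm contrast on visits is exposed to differential classification as a result. The documents do not show that such bias would occur, and its size cannot be computed from them. Under the stated assumptions, shifts of a few points in the coded share would move the rate ratio noticeably and raise the pairwise false-positive rate above 5%.

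The weight is moderate. Visits are in the *Study design* hypotheses and are the sole bio-medical marker, but they are not among the primary or secondary outcomes in the Abstract.

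On patient blinding, only a wording correction is warranted. The sentence is too broad for the empty arm, and self-reported contrasts with that arm should be read as not fully blinded.

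**What to change.** **Visit coding.** Change the sentence on who codes the visits. Forms should carry only a study number, with identifying details removed. Existing staff without access to the arm list should do the coding. The research investigator may do it if the forms are de-identified and patients cannot be recognised from them; this condition matters because *Experimental and clinical protocol* has that role screening and informing patients. Lock the coded file before the arm list is linked. Any forms already coded can be recoded from the originals in the same way.

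**Blinding sentence.** Qualify it to say that patients are not told of the randomization, the other conditions or the expected benefits, that patients in the empty-control arm know they do no writing, and that self-reported contrasts with that arm are interpreted as not fully blinded.

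**Cost.** The coding change needs relabelled forms and a fixed order of coding, locking and linking. It needs no new staff, no change to the sample size and no change to the hypotheses. The second change is wording only.
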